## 9.0 Setting

As this is an observational, non-interventional study, patient's treatments are determined solely by the treating physician, which falls within the scope of the physician's/institution's general liability insurance coverage and precedes the decision to offer the patient the opportunity to participate in the study.

According to the requirements for non-interventional or observational studies, no additional diagnostic or monitoring procedures will be applied to the patients included in the study other than those which would ordinarily be applied in the course of the particular therapeutic strategy.

### Site and Researcher Selection

The research sites will be community or hospital based medical centers experienced in the treatment of RA.

Researchers will have access to RA patient population and have the ability to appropriately conduct the study in accordance with applicable legal and regulatory requirements.

### Patient Selection Criteria

Patient attending a routine visit, who fulfill ALL the following selection criteria, can be included:

- Male or female.
- Adult (aged  $\geq 18$  years).
- Has rheumatoid arthritis (RA), diagnosed either by the 1987-revised ACR classification criteria or by the 2010 ACR / EULAR classification criteria for RA.
- Currently treated with any kind of approved csDMARDs, tsDMARDs or bDMARDs.
- Has been exposed to no more than 2 bDMARDs at the time of the enrollment.
- His/her RA is sub optimally controlled, despite full tolerable dose of current DMARD therapy administered for  $\geq 3$  months.

- Definition of suboptimal disease control: having high or moderate disease activity (as defined by having DAS28 > 3.2) for at least 1 month but not more than for 4 months prior to the enrollment.
- Understands the language and willing/able to complete the patient reported outcome questionnaires.
- Does not participate in any kind of clinical study for RA.
- Has provided written authorization to the investigator to use and/or disclose personal and/or health data, or informed consent if requested by the local regulations.

## 9.1 Variables

Copyright protected outcome measures and patient questionnaires are listed in Appendix 1.

### 9.1.1 Disease activity measured by DAS28CRP, CDAI and SDAI

Composite indices or pooled indices are useful tools for the evaluation of disease activity in patients with rheumatoid arthritis (RA). They allow the integration of various aspects of the disease into a single numerical value, and may therefore facilitate consistent patient care and improve patient compliance, which both can lead to improved outcomes. The DAS score [66] measures a patient's level of disease activity at a given time using tender joint count (TJC), swollen joint count (SJC) across 44 joints, ESR or CRP and patient's health assessment along a VAS (0-100 mm).

The DAS28 score is a modified version that is scored across a reduced set of 28 joints, omitting the feet. As Disease Activity Score 28-joint count (DAS28) is currently the most commonly used composite measure of RA disease activity in clinical practice, remission and low disease activity will be defined as follows [67]:

- Remission if DAS28 score < 2.6.
- Low disease activity (LDAS) if DAS28 score  $\leq$  3.2.
- Moderate disease activity if DAS28 score is > 3.2 -5.1.
- High disease activity if DAS28 score is > 5.1.

In this study, DAS28CRP is preferred since it is frequently used in clinical research, due to several reasons. Firstly, CRP measurements are routinely used in clinical practice, and are often available in

circumstances when ESR measurements are not. CRP levels are more sensitive to short-term changes in disease activity [68], whereas ESR can be influenced by a number of unrelated factors, such as age, gender or plasma proteins. Lastly, laboratory tests used to calculate CRP are faster than those used to measure ESR, and measurements can be standardized in a central laboratory for multicenter clinical trials. Due to variability of practice across participating countries, DAS28ESR will be accepted.

The Simplified Disease Activity Index (SDAI) and the Clinical Disease Activity Index (CDAI) [69, 70] are two new tools for the evaluation of disease activity in RA. They have been developed to provide physicians and patients with simple and more comprehensible instruments. Moreover, the CDAI is the only composite index that does not incorporate an acute phase response and can therefore be used to conduct a disease activity evaluation essentially anytime and anywhere. These two new tools have not been developed to replace currently available instruments such as the DAS28, but rather to provide options for different environments.

#### Cut-points of SDAI:

- High disease activity > 26
- Moderate disease activity > 11 - 26
- Low disease activity > 3.3 - 11
- Remission  $\leq 3.3$

#### Cut-points of CDAI

- High disease activity > 22
- Moderate disease activity > 10 - 22
- Low disease activity  $\geq 2.8$  - 10
- Remission  $\leq 2.8$

### 9.1.2 Morning stiffness and Joint pain

Although morning stiffness is not specific to RA, changes in morning stiffness for an individual patient are helpful when monitoring health status. Health professionals can ask about morning stiffness but the

most accurate and consistent approach to assessment from one visit to the next appears to be a patient self-report questionnaire.

In this study, a visual analogue scale using numeric rating scale (NRS) will be used to assess severity and length of morning stiffness in the past 7 days. Similar NRS will be employed to assess the worst joint pain in the past 7 days prior to the study.

### **9.1.3 HAQ-DI**

**Health Assessment Questionnaire (HAQ)** is a widely accepted, validated, rheumatology specific instrument to assess physical function in RA [71]. It consists of 20 questions, covering eight types of activities. For each question, scores range from 0 to 3 (0 = without any difficulty; 1 = with some difficulty; 2 = with much difficulty or with assistance; 3 = unable to do). HAQ Disability Index (HAQ-DI) score is the average of the highest score in each of the eight categories.

### **9.1.4 FACIT-F version 4**

Although there are several validated tools for the measurement of fatigue, there is no gold standard. One self-report questionnaire that has been validated for use with older adults is the Functional Assessment of Chronic Illness Therapy (FACIT) Fatigue Scale (Version 4). The FACIT Fatigue Scale is a short, 13-item, easy to administer tool that measures an individual's level of fatigue during their usual daily activities over the past week. The level of fatigue is measured on a four point Likert scale (0 = not at all fatigued to 4 = very much fatigued) [72]. The FACIT Fatigue Scale is one of many different FACIT scales that are part of a collection of health-related quality of life (HRQOL) questionnaires targeted to the management of chronic illness referred to as The FACIT Measurement System. The group tests newly constructed FACIT subscales on a sample of at least 50 subjects. The FACIT tool has been translated in more than 45 different languages permitting cross-cultural comparisons.

### **9.1.5 TSQM version 1.4**

Although numerous disease-specific measures of patients' treatment satisfaction for medication have been reported in the literature, less attention has been paid to developing a more general measure of TSQM one that would permit comparisons across medication types and patient conditions. To fill this gap, the TSQM was developed [51, 73]. TSQM is a generic measure of treatment satisfaction for medication, was rigorously developed with sound psychometric properties. Multiple linguistically

validated languages available. Three versions are available: **TSQM Ver 1.4** (14 items), TSQM Ver II (11 items), and TSQM Ver 9 (9 items).

Domains include: Effectiveness, Side effects, Convenience, Global Satisfaction. This measure attempts to show that adherence is expected to be related with patients' satisfaction with therapy and such satisfaction can be a function of not only the effect of the treatment, but also the services offered. In the study, TSQM-1.4 will be employed.

### **9.1.6 Self-Reported Adherence (Appendix 2)**

The terms “adherence” and “compliance” are often used interchangeably, however adherence is becoming the preferred term as it suggests the patient has a less passive role in the management of their medication [34].

In this study a 0-100 mm VAS will be employed to gain numeric insights about patients’ estimation of drug intake adherence.

Visual analog scales (VASs) have been extensively used for assessment in a number of health domains (e.g., acute and chronic pain) and have recently been applied to assessment of antiretroviral therapy medication adherence [74]. It has been shown that patients’ self-evaluation of drug intake evaluated by VAS scores correlates with objective adherence measures and thus can be a valuable, easy to use tool for assessing adherence in IMIDs in routine clinical practice [40, 74, 84].

### **9.1.7 WPAI-RA**

The Work Productivity and Activity Impairment (WPAI) Questionnaire [75] was created as a patient-reported quantitative assessment of the amount of absenteeism, presenteeism and daily activity impairment attributable to general health (WPAI-GH) or a specific health problem, such as RA (**WPAI-SHP, WPAI-RA**). The WPAI-GH and the WPAI-SHP were created simultaneously and use the same template, but in the GH version the subject is instructed to respond with reference to the general health status while in the SHP version the subject responds with reference to a specified health problem, disease (RA) or condition. The following 4 outcomes will be expressed as a percentage from 0 to 100:

- % Presenteeism – percentage of impairment while working due to the respective IMID.
- % Absenteeism – percentage of work time missed due to the respective IMID.

- % Total work productivity impairment (TWPI) – percentage of overall work impairment due to the respective IMID
- % Total activity impairment (TAI) – percentage of general (non-work) activity impairment due to the respective IMID.

The percentage of work time missed (absenteeism) is calculated as  $Q2 / (Q2 + Q4) \times 100\%$ . The percentage of impairment while working (i.e. presenteeism) is calculated as  $Q5/10 \times 100\%$ . The percentage of total work productivity impairment ((TPI) i.e., work productivity loss) is  $Q2 / (Q2 + Q4) + (1 - Q2 / (Q2 + Q4)) \times (Q5/10) \times 100\%$ . The percentage of total activity impairment (TAI) is calculated as  $Q6/10 \times 100\%$ .

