### **9.5.2 Secondary variables**

The secondary variables are:

- Sociodemographic, medication and disease characteristics including RA disease activity scores of DAS28, CDAI/SDAI and proportion of patients with high or moderate disease activity as per DAS28, CDAI/ SDAI.
- Proportion of patients in which treating physician is going to switch the DMARD therapy. Proportion of different mode of action of next planned DMARD.
- Effectiveness, Side effects, Convenience, Global Satisfaction sub scores of TSQM 1.4.
- Total fatigue score measured by FACIT-F.
- RA functional capacity score of HAQ-DI.
- Duration and severity of morning stiffness scores.
- Worst reported pain score.
- Self-reported adherence score (VAS).
- Total score and individual components of WPAI-RA score (% Presenteeism, % Absenteeism, % Total work productivity impairment, % Total activity impairment).
- General quality of life Total score, PCS-score and MCS-score domains and scale scores of SF-36v2 for the full study population.
- Total Electronic health literacy scale score as measured by eHEALS for the full study population.

- Health resource utilization assessment scores in 12 months preceding the study inclusion for the full study population.
- Proportion of patients with different level of patients' need of PSP support for each question point as measured by AbbVie developed questionnaire
- Proportion of patients for each question point about patients' medication preferences as measured by AbbVie developed questionnaire
- Proportion of patients with different level of patients' treatment expectations for each question point as measured by AbbVie developed questionnaire

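### Section 9.1.7: the total work productivity impairment formula lacks an outer bracket, so coding it with ×100 makes the score too low by 99 × Q2/(Q2+Q4) points

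*Protocol*

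**What the plan says.** Protocol Section 9.1.7 introduces the WPAI-RA results with "The following 4 outcomes will be expressed as a percentage from 0 to 100". It describes total work productivity impairment as "percentage of overall work impairment due to the respective IMID" and then gives a scoring formula for each outcome. For absenteeism, presenteeism and activity impairment, the factor 100% multiplies the whole expression. For total work productivity impairment the formula reads "Q2 / (Q2 + Q4) + (1 - Q2 / (Q2 + Q4)) \times (Q5/10) \times 100", followed by a per cent sign. No bracket encloses the two added terms.

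Section 9.5.2 makes this outcome a secondary variable: "Total score and individual components of WPAI-RA score (% Presenteeism, % Absenteeism, % Total work productivity impairment, % Total activity impairment". Section 9.5.3 plans subgroup comparisons of all the listed measures where subgroups are large enough. No other section of the protocol restates or corrects the formula.

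**The concern.** Under the usual order of operations, a multiplier at the end of a sum acts only on the last term. Coded with 100, the printed formula adds a fraction (share of work time missed, 0 to 1) to a number on a 0 to 100 scale (impairment during the remaining time). The result is not on the scale the section asks for and does not measure overall impairment.

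The error is not a constant rescaling that a reader could undo. Its size depends on each patient's absence, so it biases the mean downward and distorts comparisons between groups that differ in absence. Such a contrast can shrink or change sign. Work ability is part of the research question in Section 7.0, and the WPAI-RA is the instrument listed for it in Section 8.1.

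**Working it through.** **Inputs.** From Section 9.1.7: A = Q2/(Q2+Q4), the fraction of work time missed, and P = Q5/10, the impairment while working. The protocol gives no worked WPAI value, so there is no published figure to reproduce. The hours below are illustrative and assume a 40-hour week.

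**The two forms.**
- Printed, coded with ×100: T₁ = A + (1 − A) × P × 100
- With the outer bracket: T₂ = [A + (1 − A) × P] × 100
- Shortfall: T₂ − T₁ = 100A − A = 99A points, whatever the value of P. It is zero only when Q2 = 0.

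**Numbers put in.**

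| Q2 (h missed) | Q4 (h worked) | Q5 | A | P | Printed, ×100 | Bracketed | Shortfall |
|---|---|---|---|---|---|---|---|
| 0 | 40 | 5 | 0.00 | 0.5 | 50.0 | 50.0 | 0.0 |
| 4 | 36 | 4 | 0.10 | 0.4 | 36.1 | 46.0 | 9.9 |
| 8 | 32 | 5 | 0.20 | 0.5 | 40.2 | 60.0 | 19.8 |
| 10 | 30 | 4 | 0.25 | 0.4 | 30.25 | 55.0 | 24.75 |
| 20 | 20 | 5 | 0.50 | 0.5 | 25.5 | 75.0 | 49.5 |
| 20 | 20 | 0 | 0.50 | 0.0 | 0.5 | 50.0 | 49.5 |
| 40 | 0 | any | 1.00 | any | 1.0 | 100.0 | 99.0 |

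Third row in full: 0.2 + 0.8 × 0.5 × 100 = 40.2, against (0.2 + 0.8 × 0.5) × 100 = 60.0.

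**Direction.** The slope in A is 1 − 100P for the printed form and 100(1 − P) for the bracketed form. The printed slope is negative once P exceeds 0.01. At P = 0.5 it is −49, where it should be +50. At P = 0 it is +1, where it should be +100.

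**Effect on a contrast.** Compare the second and fourth rows, which share P = 0.4. The patient with more absence should score 55.0 − 46.0 = 9.0 points higher, but the printed form gives 30.25 − 36.1 = −5.85. In general, a contrast between two groups moves by 99 times their difference in mean A.

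**Internal check.** A correct total cannot be below either component, because A + (1 − A)P ≥ A and A + (1 − A)P = P + A(1 − P) ≥ P. Over the grid Q2 = 0 to 40, Q4 = 40 − Q2, Q5 = 0 to 10 (41 × 11 = 451 points), the printed form falls below the patient's own absenteeism percentage at 311 points. That counts answer combinations. It does not estimate how many patients would be affected.

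**The other reading.** If 100% is taken strictly as the number 1, the printed expression is A + (1 − A)P. With A = 0.2 and P = 0.5 this is 0.60, that is 60%, which is correct as a proportion.

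**The case against.** The strongest reply is that 100% equals 1, so the formula as printed is arithmetically right. On that strict reading it is. But the section asks for values from 0 to 100, and the usual way to get there is to code the factor as 100. A rule that is right on one reading and wrong by up to 99 points on another is not a safe specification.

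A second reply is that this is an evident typographical slip whose intent is plain from the stated scale and the neighbouring formulas, and that a separate SAP may score it correctly. This largely stands: nothing in the documents shows that any program contains the error. Even so, the protocol states a scoring rule rather than leaving it open. Amendment 1 listed Section 9.1 and typographical corrections (Section 4.0), yet the current text still carries the slip.

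A reader might infer three stronger things that the documents do not support:
- *That absenteeism nearly vanishes from the score.* Only the added term shrinks. Absence still acts through the factor (1 − A).
- *That patient rankings reverse throughout.* With Q5 = 0 the score still rises with absence, only compressed, and with Q2 = 0 the two forms agree.
- *That the planned regressions would be wrong.* Section 9.5.3 names satisfaction, adherence, preferences, expectations, support needs and DMARD switching as the outcomes to be related to patient characteristics. It does not name WPAI as a response.

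**Conclusion.** The formula needs correcting. Coded with ×100, it understates total work productivity impairment by 99 × Q2/(Q2+Q4) points for every patient who missed any work: 19.8 points at 20% absenteeism, 49.5 at 50%, and 99 in the extreme case of no hours worked. Above 1% presenteeism, the score moves the wrong way as absence rises.

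This rests on normal operator precedence and on coding 100% as 100. The documents give no distribution of absence, so the bias in the study mean cannot be stated beyond 99 times the mean of A among patients with a score.

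A reader might infer a serious threat to the study, but the scope is narrow. One component of one secondary variable is affected, together with its subgroup summaries. Section 9.7 treats secondary p-values as descriptive and subgroup comparisons as exploratory. The other three WPAI outcomes are correctly scaled. The primary endpoint and the sample size both rest on the TSQM and do not change. Severity: a minor to moderate correction.

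**What to change.** In Section 9.1.7, write

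TWPI = {Q2/(Q2+Q4) + [1 − Q2/(Q2+Q4)] × (Q5/10)} × 100%

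and confirm that the derivation program uses this form. The abbreviation in that sentence (TPI) can be aligned with TWPI, as listed in Section 1.0, at the same time; that is cosmetic. A useful but optional program check is that the total is never below the patient's absenteeism or presenteeism percentage.

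The cost is one bracket pair in the protocol and a short check of the program. No new data are needed: if the item responses are stored, the score can be recalculated at any time.

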### **9.1.8 SF-36 version 2**

Sort Form -36 version 2 is a multi-purpose, short-form health survey with only 36 questions [76]. It yields an 8-scale profile of functional health and well-being scores as well as psychometrically-based physical and mental health summary measures and a preference-based health utility index. It is a generic measure, as opposed to one that targets a specific age, disease, or treatment group. Accordingly, the SF-36 has proven useful in surveys of general and specific populations, comparing the relative burden of diseases, and in differentiating the health benefits produced by a wide range of different treatments. In 1996, Version 2.0 of the SF-36 (SF-36v2) was introduced, to correct deficiencies identified in the original version. Those improvements were implemented after study using both qualitative and quantitative methods. The SF-36v2 has 2 summary scores, the Physical Component Summary (PCS) and Mental Component Summary (MCS) scores, and 8 domain scores: physical function, bodily pain, role limitations–physical, general health, vitality, social function, role limitations–emotional, and mental health. Domain scores range from 0 to 100, with greater scores reflecting better health status. The SF-36v2 summary and domain scores have excellent reliability and good construct validity across the general population as well as chronic disease populations including RA.

### **9.1.9 eHealth Literacy Scale**

The eHealth Literacy Scale (eHEALS) has been developed to address the need to assess eHealth literacy for a wide range of populations and contexts [41]. The eHEALS is a self-report tool that can be administered by a health professional and is based on an individual's perception of her or his own skills

and knowledge within each measured domain. The instrument is designed to provide a general estimate of consumer eHealth-related skills that can be used to inform clinical decision making and health promotion planning with individuals or specific populations.

#### **9.1.10 Questionnaires to assess patient needs for support via PSP, medication preferences and treatment expectations (Appendices 3, 4, 5)**

The questionnaires being used in this study are developed by AbbVie based on the available literature and patient research [39, 48, 53, 77-79] due to limited availability of appropriate validated tools.

#### **9.1.11 Health care resource utilization (HRU) (Appendix 6)**

**Health resource utilization** 12 months preceding the study inclusion will be assessed as follows:

- Number of visits by a health care professional for RA in the past 3 months.
- Number and length of hospitalizations in the past 3 months.
- Number of emergency visits in the past 3 months.

To obtain 12-month health care resource utilization and sick leave before the enrollment, the collected 3-month data will be multiplied by 4. The rationale for this approach is that a similar percentage of patients would consume these quantities of resources in any given 3-month period, and it avoids memory bias [80-82].

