## 6.0 Rationale and Background

### 6.1 Background

Rheumatoid arthritis (RA) is a chronic inflammatory disease which, if not controlled properly, may result in severe and progressive articular injury, loss of function, deterioration of the quality of life, and increased mortality [1-4]. Biological disease modifying drugs (bDMARDs) are typically used as second-line therapy in patients with an inadequate response to conventional synthetic disease modifying drugs (csDMARDs). The group of targeted synthetic DMARDs (tsDMARDs) represents a novel therapeutic option for patients with inadequate response to cs/bDMARDs [13-22]. However, the role of tsDMARDs in current treatment paradigm is not yet fully established, partially since we still have limited data on their real-world effectiveness and on the factors associated with sub-optimal response to them [23].

Despite the fact that the range of treatment options is steadily increasing and RA therapies help to slow down disease progression and the development of joint damage, many patients with RA remain sub-optimally managed with sustained remission rarely achieved [5-11]. Two-thirds of RA patients do not respond adequately to their initial bDMARD, and sustained clinical remission is achieved in only 20–40% of patients treated with DMARDs [5, 6]. Moreover, radiographic progression can still occur even in the presence of clinical remission [12]. Suboptimal management of RA results in increased healthcare resource use and medical costs [9].

**Treatment adherence** is of particular importance in RA as it is characterized by fluctuating and usually progressive disease courses and a need for lifetime management [27-32]. Despite the fact that the efficacy of available medications is proven even with long term use [37-39], the level of adherence is still suboptimal among RA patients, varying from 30 to 80% [4,33], thus resulting in suboptimal outcomes and representing a significant financial burden to health care [34-36,42-43]. There is evidence available confirming that bDMARD use is associated with better adherence than conventional oral DMARDs in RA [40].

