## 7.2 Secondary Objectives

- To assess the sociodemographic, clinical, functional, adherence and quality of life characteristics of sub optimally controlled RA patients treated with conventional/targeted synthetic or biological DMARDs.
- To assess healthcare resource utilization (HRU) during 12 months prior to enrollment to the study in sub optimally controlled RA patients treated with conventional/targeted synthetic or biological DMARDs.
- To assess electronic health literacy of sub optimally controlled RA patients treated with conventional/targeted synthetic or biological DMARDs.
- To assess expectations towards RA therapy, medication preferences and needs for patient support of sub optimally controlled RA patients treated with conventional/targeted synthetic or biological DMARDs
- To determine relationship between treatment satisfaction, its subdomains and patient characteristics.
- To determine relationship between adherence and patient characteristics.
- To determine relationship between medication preferences and patient characteristics.
- To determine relationship between treatment expectations and patient characteristics.
- To determine relationship between specific PSP-related needs and patient characteristics.
- To evaluate subgroups of patients, if there are sufficient patients in each subgroups:

- To evaluate the above measures in the subgroups of patients treated with different treatment modalities, regimes and line therapy and route of administration (e.g. patients treated with csDMARDs, bDMARDs, tsDMARDs; patients treated with orally or parenterally administered DMARDs (SC or IV), patients treated in monotherapy, patients treated with combination therapy, patients treated with first or second line bDMARD).
- To evaluate the above measures in subgroups of patients with different clinical characteristics (e.g. with high or moderate disease activity).
- To evaluate the above measures between the subgroups of patients with and without comorbidities including cardiovascular comorbidities.
- To understand treating rheumatologists' treatment strategy in the study population and its relationship with patient characteristics.

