## Appendix 6: Health care resource utilization (HRU) in the past 3 months from enrollment

In the past 3 months, has the subject had any medical visits for their rheumatoid arthritis (RA) ?

YES: \_\_\_\_

NO: \_\_\_\_

If YES, please provide the following:

1. In the past 3 months, has the subject been seen by a health care professional for their RA?

YES: \_\_\_\_

NO: \_\_\_\_

If YES, how many times: \_\_\_\_

2. In the past 3 months, has the subject been seen in the Emergency Room for their RA?

YES: \_\_\_\_

NO: \_\_\_\_

If YES, how many times: \_\_\_\_

3. In the past 3 months, has the subject been admitted to the hospital due to their RA?

YES: \_\_\_\_

NO: \_\_\_\_

If YES, please list the ADMISSION DATE: \_\_\_\_/\_\_\_\_/\_\_\_\_

DD MMM YYYY

DISCHARGE DATE: \_\_\_\_/\_\_\_\_/\_\_\_\_

DD MMM YYYY

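### Twelve-month resource use is 3-month use multiplied by 4, from a look-back window that the entry criteria enrich for active disease

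*Protocol*

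**What the plan says.** The secondary objective in section 7.2, repeated in the abstract (3.0), is "To assess healthcare resource utilization (HRU) during 12 months prior to enrollment to the study". The matching secondary variable in 9.5.2 also covers 12 months. The data collected cover 3 months (8.1, 9.1.11, Appendix 6).

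Section 9.1.11 bridges the gap with this rule: "To obtain 12-month health care resource utilization and sick leave before the enrollment, the collected 3-month data will be multiplied by 4". Its reason is that "a similar percentage of patients would consume these quantities of resources in any given 3-month period, and it avoids memory bias", with three cited sources.

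Three other places bear on the rule:

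- The Patient Selection Criteria (9.0) require DAS28 > 3.2 "for at least 1 month but not more than for 4 months prior to the enrollment".
- Section 6.1 says: "Suboptimal management of RA results in increased healthcare resource use and medical costs".
- Appendix 6 asks for a count of health-professional visits (item 1) and emergency visits (item 2). For hospital stays (item 3) it has a yes/no box and then "If YES, please list the ADMISSION DATE", with one discharge date and no count. Section 9.1.11 wants both the number and the length of hospitalizations.

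For resource use, the limitations in 9.7 mention recall bias but not the extrapolation.

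**The concern.** Multiplying by 4 gives the right 12-month mean only if the three earlier quarters were, on average, like the last one. This study picks its patients by what happened in the last quarter. Every patient must have had active disease for at least the final month of the window, and the current active state may have begun no more than 4 months ago. If use is higher while disease is active, as section 6.1 suggests, the factor 4 projects an unusually heavy quarter onto the whole year.

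A second problem remains even if average use is flat over the year. The stated reason concerns the percentage of patients using resources in a quarter. At most that supports scaling a group mean. Section 9.5.3 summarises continuous variables by SD, quartiles and range, and categorical variables by proportions, and those do not scale this way.

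Third, two of the quantities to be annualised may not be available: sick leave is not among the listed items, and the hospital item as printed does not ask how many stays there were. At stake is a named secondary objective, reported for a period that the study does not observe.

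**Working it through.** **The plan's figure.** 12 months / 3 months = 4. The factor is arithmetically right; the question is what it assumes.

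**Bias of the mean.** Inputs:

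- a = months of current active disease before enrollment, 1 to 4 (Patient Selection Criteria).
- R = monthly use while active divided by monthly use while not active. The protocol gives no value, so 1 to 3 is an assumed range.
- The other 12 − a months are first assumed not active. The protocol does not say this.

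In units of non-active monthly use:

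- Multiplied value = 4 × (min(a,3) × R + 3 − min(a,3))
- 12-month value = a × R + 12 − a

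For R = 2 and a = 1: 4 × (2 + 2) = 16 against 2 + 11 = 13, ratio 1.23. For R = 2 and a = 3: 4 × 6 = 24 against 6 + 9 = 15, ratio 1.60.

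| R | a = 1 | a = 2 | a = 3 | a = 4 |
|---|---|---|---|---|
| 1 | 1.00 | 1.00 | 1.00 | 1.00 |
| 1.5 | 1.12 | 1.23 | 1.33 | 1.29 |
| 2 | 1.23 | 1.43 | 1.60 | 1.50 |
| 3 | 1.43 | 1.75 | 2.00 | 1.80 |

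Put differently, the window holds 1 to 3 active months. Multiplying by 4 implies 4 to 12 active months a year, against 1 to 4 in the current episode.

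**Sensitivity to earlier flares.** Assume a is uniform on 1 to 4 months. The mean of a is 2.5 and the mean of min(a,3) is 2.33. With R = 2 and no other active time, the ratio is 4 × (3 + 2.33) / (12 + 2.5) = 21.33/14.5 = 1.47. With 4 further active months earlier in the year (assumed), it is 21.33/18.5 = 1.15.

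**Distribution with stable average use.** Let s be the SD of use in one quarter and r the correlation between any two quarters within a patient.

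- SD of the multiplied value: 4s.
- SD of the sum of four quarters: s × sqrt(4 + 12r).
- Ratio: 4/sqrt(4 + 12r), which is 2.0 at r = 0, 1.45 at r = 0.3, 1.26 at r = 0.5, and 1.0 only at r = 1.

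Multiplied counts can only be 0, 4, 8 and so on. If 5% of patients have an admission in a quarter (assumed), multiplication leaves 5% with any admission. Over four independent quarters it would be 1 − 0.95^4 = 18.5%; with positive correlation it lies between 5% and 18.5%.

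**Items on the form.** Sick leave appears in the rule in 9.1.11, but not in that section's three bullets, in the data list in 8.1 or in Appendix 6. The WPAI-RA (9.1.7) yields absenteeism as a percentage of work time, not an amount of sick leave over 3 months. For hospital stays, suppose only one per patient is recorded and admissions are Poisson with mean m per 3 months. The share captured is (1 − exp(−m))/m: 99% at m = 0.02 and 91% at m = 0.2 (both assumed). About 1% to 9% of admissions would then be lost.

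**The case against.** Several points on the other side are sound.

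- **Earlier months.** A reader might infer from the 4-month cap that the rest of the year was free of active disease. The criterion limits only the duration of the current state. Section 6.1 describes RA as fluctuating, and up to two prior bDMARDs are allowed, so earlier active periods are possible and would shrink the bias. Only 1 of the 3 window months must be active.
- **Size.** A reader might take one figure, such as 47%, as the bias. It rests on an assumed rate ratio, an assumed spread of durations and a quiet rest of the year. Section 6.1 gives a direction, not a ratio, and routine follow-up visits need not track activity at all.
- **SD.** A reader might conclude that the SD is doubled. That is the independence case; lasting differences between patients make the ratio smaller.
- **Transparency.** The rule, its reason and its sources are stated openly, and the data are labelled as 3-month data. Nothing supports the reading that an extrapolated figure is being disguised. The cited sources were not available for this review.
- **Form.** A reader might conclude that repeat admissions cannot be recorded. Only the printed template is visible; the eCRF may allow repeat entries.
- **Reach.** Sick leave is in no objective and is not a listed secondary variable. The primary endpoint and the sample size are untouched, and multiplying by a constant leaves subgroup p-values unchanged.

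These points limit the size and the severity. They do not supply the similarity between quarters that the rule needs, or make a multiplied quarter into a 12-month distribution.

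**Conclusion.** The concern holds in moderate form. The assumption behind the factor 4 sits badly with the protocol's own entry criteria, and the annualised mean is probably too high. The upward direction rests on use being higher while disease is active, which section 6.1 supports. The size is open: no bias at R = 1, about 23% to 60% too high at R = 2 with the rest of the year not active, and less with earlier flares.

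The distributional fault does not depend on any rise in use with activity. Unless each patient's use is the same in every quarter, the SD is too large, and proportions with any use remain 3-month proportions.

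The sick-leave gap is certain on the text but minor. The admission-count gap is certain only for the form as printed.

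This should be fixed before reporting. It concerns one secondary, descriptive objective and does not threaten the study's main result.

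**What to change.** 1. In 3.0, 7.2, 9.1.11 and 9.5.2, define resource use as use in the 3 months before enrollment. Report counts, proportions and length of stay on that scale.
2. If an annual figure is still wanted, give it only as a group mean, labelled as an extrapolation from a window selected for active disease. Do not derive patient-level 12-month values.
3. Add the extrapolation to the limitations in 9.7.
4. Delete sick leave from 9.1.11.
5. Confirm that the eCRF captures repeat admissions. If it does not, report any admission and the length of the recorded stay in place of the number of hospitalizations.

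The cost is mainly wording, and the sponsor gives up the 12-month figure. New form fields would be a poor remedy at this stage. Each patient has a single visit, the amendment is dated 18 March 2019 and data collection was planned to end on 31 May 2019, so added items would be missing for patients already seen. Reporting on the 3-month scale needs no new data.
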